
**Institutional Review Board (IRB)**  
**Department of Physiotherapy & Rehabilitation**  
**Jashore University of Science & Technology**

mail: [[contact]](mailto:[contact]) website: <https://ptr.just.edu.bd/>

|                                   |                                                                                                                                                                                                                                                   |
|-----------------------------------|---------------------------------------------------------------------------------------------------------------------------------------------------------------------------------------------------------------------------------------------------|
| Principal investigator (s) | [name]
Department of Physiotherapy and Rehabilitation, JUST
Email: [contact]                                                                                    |
| Funding source (s)         | This study received partial funding for data collection and intervention from the University Grants Commission through the Physiotherapy and Rehabilitation Department, Jashore University of Science and Technology (JUST), Jashore, Bangladesh. |
| Ethical considerations     | All participants will provide written informed consent before enrollment. The study will adhere to the ethical guidelines outlined in the Declaration of Helsinki.                                                                                |

## 5. Annexure: E – Questionnaire

### Section I

Personal details & socio-demographic status

Lifestyle information

Health and Medical Background

### Section II

#### ***Primary Outcome Measures***

Go/No-Go (GNG) Task

Trail Making Test (TMT)

Corsi Block Tapping Task (CBTT)

Forward Digit Span (FDS) Test

Backward Digit Span (BDS) Test

#### ***Secondary Outcome Measures***

Social Responsiveness Scale, Second Edition (SRS-2)

Autism Treatment Evaluation Checklist (ATEC)

**6. Annexure: F – Intervention Tracking Sheet/Checklist**  
**7. (Put a tick ✓)**

| Patient ID | Group | Start date | Intervention Timeline
Session: 1 to 60 | End date | Any comments |
|------------|-------|------------|-------------------------------------------|----------|--------------|
|            |       |            |                                           |          |              |

**7. Annexure: G – Adverse Effect Checklist**  
(Put a tick ✓ and write a comment if any adverse effect notices, and put a cross X mark if no adverse effect notice)

| Patient ID | Group | Pretest | Intervention | Post-test | Follow-up |
|------------|-------|---------|--------------|-----------|-----------|
|            |       |         |              |           |           |

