| Intervention details | All participants will receive a healthy-lifestyle guideline booklet to follow throughout the 24-week study. The wait-list control group will receive these guidelines plus biweekly discussion sessions during their initial 12-week period and will later receive the same intervention as the experimental group. The experimental group will complete a 12-week, five-component multimodal program delivered by trained physiotherapists, with                                                                                                                                                                                                                                                                                                                                                                                                                     |

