|                              | all procedures, dosages, and progressions monitored by four research assistants for consistency. Each 60-minute session, conducted five times per week in small groups, will include yoga (10 minutes), aerobic exercise (15 minutes), strengthening exercises (10 minutes), neurocognitive tasks (15 minutes), and music-based mindfulness (10 minutes), with structured rest intervals and progressive adjustments based on individual abilities. Detailed intervention content is presented in a supplementary file. A follow-up assessment will occur 12 weeks after the intervention to evaluate sustained effects, during which all participants will continue following lifestyle guidelines, and the control group will undergo the experimental intervention, accompanied by two discussion sessions addressing the health needs of children with ASD. |
| Intervention provider | Experienced and qualified health professionals                                                                                                                                                                                                                                                                                                                                                                                                                                                                                                                                                                                                                                                                                                                                                                                                                  |

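### Annexure G records adverse effects only when one is noticed, with no common question and no code for a child who was not asked, while scheduled contact differs widely between the two ASD arms

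*Protocol*

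**What the plan says.** **The form.** Annexure G instructs staff: "Put a tick ✓ and write a comment if any adverse effect notices", and otherwise "put a cross X mark if no adverse effect notice". Its columns are "Patient ID | Group | Pretest | Intervention | Post-test | Follow-up", so there is one cell per child per phase. It gives no wording of a question, no recall window, and no entry for a child who was not seen or has withdrawn.

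**Contact in weeks 1 to 12.** Annexure B (Intervention details) states: "The experimental group will complete a 12-week, five-component multimodal program". Its sessions are "conducted five times per week in small groups", and the tracking sheet in Annexure F runs over "Session: 1 to 60". Over the same weeks the wait-list arm has "biweekly discussion sessions during their initial 12-week period", in addition to the lifestyle booklet that everyone receives.

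**Contact in weeks 13 to 24.** In the follow-up period "the control group will undergo the experimental intervention".

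The statistical section of Annexure B describes no analysis of adverse effects.

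**The concern.** A rule based on noticing makes the record depend on how often someone is in a position to notice. With equal true event rates, the arm that is seen more often will show more ticks. Short-lived events such as a minor fall, soreness or a day of distress are the most exposed. They can come and go between two fortnightly contacts but will seldom be missed by someone who sees the child five days a week.

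The second weakness is that a cross can mean that nothing happened or that nobody was there to see. If a child leaves because of something that happened at home, the form has no entry to show that the question was never put.

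At stake is whether the form can support a statement about harm by arm. This cannot be left to an analysis plan, because later analysis cannot separate *none* from *not asked* if the form never recorded the difference.

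**Working it through.** **1. Contacts in weeks 1 to 12.**
- Experimental arm: 5 sessions a week × 12 weeks = 60. This reproduces the number on the Annexure F tracking sheet.
- Wait-list arm: 12 / 2 = 6 if *biweekly* means every two weeks, or 2 × 12 = 24 if it means twice a week. The protocol does not define the word.
- Ratio of scheduled contacts: 60 / 6 = 10, or 60 / 24 = 2.5.

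**2. Contacts in weeks 13 to 24.** The wait-list arm now receives the programme. For the experimental arm Annexure B mentions no programme sessions in this period, and two discussion sessions at most. The imbalance is reversed.

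**3. Effect on what is recorded.** The protocol gives no adverse effect rates, so this step is an illustration. Assumptions:
- true event rates are equal in the two arms;
- an event is recorded only if it is present on a day of contact, and is never reported later;
- the experimental arm is seen Monday to Friday;
- the wait-list arm is seen on one day in 14, or on two non-adjacent days each week.

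The detection probability for an event of D days is the share of the 14 possible start days on which the D consecutive days include at least one contact.

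| D (days) | Experimental | Wait-list, fortnightly | Wait-list, twice weekly | Ratio, fortnightly | Ratio, twice weekly |
|---|---|---|---|---|---|
| 1 | 10/14 = 0.714 | 1/14 = 0.071 | 4/14 = 0.286 | 10.0 | 2.5 |
| 2 | 12/14 = 0.857 | 2/14 = 0.143 | 8/14 = 0.571 | 6.0 | 1.5 |
| 3 | 14/14 = 1 | 3/14 = 0.214 | 12/14 = 0.857 | 4.7 | 1.2 |
| 7 | 1 | 7/14 = 0.5 | 1 | 2.0 | 1.0 |
| 14 | 1 | 1 | 1 | 1.0 | 1.0 |

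With an assumed true risk of 20% in both arms, a 2-day event would be recorded in 0.20 × 0.857 = 17.1% of experimental children. In the wait-list arm the figure would be 0.20 × 0.143 = 2.9% (fortnightly) or 0.20 × 0.571 = 11.4% (twice weekly).

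**4. One cell per child per phase.** The table applies to single events, whereas the form records any event or none. If 2-day events follow a Poisson distribution with mean m per child, the recorded risk is 1 − exp(−m × detection probability). On the fortnightly reading:
- m = 1: 0.576 / 0.133 = 4.3;
- m = 3: 0.924 / 0.349 = 2.6.

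The distortion in the any-event proportion is therefore close to 6 only when events are rare, and it shrinks as they become common.

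**The case against.** **No harm comparison is stated.** A reader might infer that the trial's harm comparison is already biased. The protocol names no safety outcome and plans no between-arm analysis of adverse effects; one may sit in an analysis plan that is not shown. The form might also be meant only to monitor effects of the programme, to which the wait-list arm is not exposed in weeks 1 to 12. This stands. The point is about what the form could support, since it carries a Group column and invites tabulation by arm.

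**Dropouts.** A reader might infer that children who leave are counted as event-free. A child nobody saw does satisfy the literal condition for a cross, but the document does not say that such a child gets one. The cell could be left blank or carry a comment. Annexure F, with its session ticks, end date and comments column, would identify a child who stopped the programme. What remains is narrower: Annexure G has no code for this case, and Annexure F does not show whether anyone asked about events after the child stopped.

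**The ratio of 6.** It needs brief events, no later reporting and the fortnightly reading. Annexure G does not say who does the noticing and does not exclude a parent's report. Events could also be mentioned at the post-test or follow-up assessment. This stands, and it is why the ratio must be given as a range. In the other direction, Annexure B does not say that the children attend the discussion sessions, so direct observation of wait-list children may be less than assumed.

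**Crossover.** Both ASD arms have a spell of programme-level contact at some point. True, but at different times, so neither 12-week period offers equal observation of the two arms.

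**Other safety data.** A reader might infer that Annexure G is the trial's only source on harms. Parts of the file are not shown and the intervention detail is in a supplement, so the point does not rest on that.

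**Conclusion.** The concern holds as a weakness of ascertainment, with a remedy cheap enough that it should be adopted. The two-code rule, the missing common question and the missing code for children not asked are on the face of the form. The contact ratio in weeks 1 to 12 is 10 or 2.5, depending on the meaning of *biweekly*, and it reverses afterwards.

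The resulting distortion depends on assumptions. For single 2-day events noticed only at a contact, a true ratio of 1 would appear as about 6 (fortnightly) or 1.5 (twice weekly). It would appear as 2.0 or 1.0 for 7-day events, and as about 1 for events that last 14 days or are reported later. I read the Intervention and Follow-up columns as weeks 1 to 12 and 13 to 24 in both ASD arms; the form does not date its phases.

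The documents do not support saying that dropouts are recorded as free of events, or that a planned harm analysis is invalid. The efficacy analyses are not affected.

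**What to change.** **Change to Annexure G.**
- Add one fixed question to the parent, asking about any injury, illness or behavioural problem since the question was last put.
- Ask it at the same interval in both ASD arms during weeks 1 to 12, and again at T2 and T3. In the wait-list arm use the existing discussion sessions. In the experimental arm use a programme session at the matching interval. Make a brief call where the child has stopped attending or the parent is not present.
- Date each reply and code it as *event*, *asked and none*, or *not asked/withdrawn*.
- Base any between-arm summary of harms on these replies, and list events seen at sessions separately.
- State whether *biweekly* means every two weeks or twice a week, so that the interval can be fixed.

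**Cost.** A one-page form change, slightly more data entry, and a few calls. In weeks 1 to 12 and at T2 and T3 most of the contacts already exist. The request stops there because the experimental arm has few scheduled contacts between T2 and T3. The downside is reliance on parent recall, over a longer window at T3, but that window is the same in both arms.

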### 8. Annexure: H – Time Frame: (Gantt Chart)

| Activity | Activity Title                   | (December 2025 - November 2026) |     |     |     |     |     |     |     |     |     |     |     |
|----------|----------------------------------|---------------------------------|-----|-----|-----|-----|-----|-----|-----|-----|-----|-----|-----|
|          |                                  | Dec                             | Jan | Feb | Mar | Apr | May | Jun | Jul | Aug | Sep | Oct | Nov |
| 1        | Proposal Formulation             |                                 |     |     |     |     |     |     |     |     |     |     |     |
| 2        | Questionnaire Formulation        |                                 |     |     |     |     |     |     |     |     |     |     |     |
| 3        | Ethical Approval                 |                                 |     |     |     |     |     |     |     |     |     |     |     |
| 4        | Trial Registration               |                                 |     |     |     |     |     |     |     |     |     |     |     |
| 5        | Publicity (Online & Offline)     |                                 |     |     |     |     |     |     |     |     |     |     |     |
| 6        | Data Collection                  |                                 |     |     |     |     |     |     |     |     |     |     |     |
| 7        | Intervention                     |                                 |     |     |     |     |     |     |     |     |     |     |     |
| 7        | Data Audit & Analysis            |                                 |     |     |     |     |     |     |     |     |     |     |     |
| 8        | Writing Progression & Completion |                                 |     |     |     |     |     |     |     |     |     |     |     |
| 9        | Research Submission & Approval   |                                 |     |     |     |     |     |     |     |     |     |     |     |

**Institutional Review Board (IRB)**  
**Department of Physiotherapy & Rehabilitation**  
**Jashore University of Science & Technology**

mail: [[contact]](mailto:[contact]) website: <https://ptr.just.edu.bd/>

|    |                                   |  |  |  |  |  |  |  |  |  |  |  |  |
|----|-----------------------------------|--|--|--|--|--|--|--|--|--|--|--|--|
| 10 | Submission for publication        |  |  |  |  |  |  |  |  |  |  |  |  |
| 11 | Disseminating through conferences |  |  |  |  |  |  |  |  |  |  |  |  |
| 12 | Disseminating through Seminars    |  |  |  |  |  |  |  |  |  |  |  |  |

EC Approved Protocol

### 9. Annexure: I – Budget

| Traits                                   | Costs            |
|------------------------------------------|------------------|
| Questionnaire printing & Measuring tools | 20,000/=         |
| Advertisement                            | 50,000/=         |
| Data Collection                          | 105,000/=        |
| Intervention materials                   | 45,000/=         |
| Intervention application                 | 336,000/=        |
| Transport                                | 50,000/=         |
| Meeting/Discussion arrangements          | 100,000/=        |
| Miscellaneous                            | 50,000/=         |
| Total                             | 756,000/= |
| 5% increment                             | 6,200/=          |
| Total, including 5% increment     | 793,800/= |

## 10. Annexure: J – Funding Document

|                                                                                                                                                                                                                                                                                                                                                                                                                                                                                                                                                                                                                                                                                                                                                                                                                                                                                                                                                                                                                                                                                                                                                                                                                                                                                                                                                                                                                                                                                                                                                                                                                                                                                                                                                                                                                                                                                                                                                                                                                  |                                                                                                                                                                                     |
|------------------------------------------------------------------------------------------------------------------------------------------------------------------------------------------------------------------------------------------------------------------------------------------------------------------------------------------------------------------------------------------------------------------------------------------------------------------------------------------------------------------------------------------------------------------------------------------------------------------------------------------------------------------------------------------------------------------------------------------------------------------------------------------------------------------------------------------------------------------------------------------------------------------------------------------------------------------------------------------------------------------------------------------------------------------------------------------------------------------------------------------------------------------------------------------------------------------------------------------------------------------------------------------------------------------------------------------------------------------------------------------------------------------------------------------------------------------------------------------------------------------------------------------------------------------------------------------------------------------------------------------------------------------------------------------------------------------------------------------------------------------------------------------------------------------------------------------------------------------------------------------------------------------------------------------------------------------------------------------------------------------|-------------------------------------------------------------------------------------------------------------------------------------------------------------------------------------|

| Reference No: JUST/PTR/2025/17                                                                                                                                                                                                                                                                                                                                                                                                                                                                                                                                                                                                                                                                                                                                                                                                                                                                                                                                                                                                                                                                                                                                                                                                                                                                                                                                                                                                                                                                                                                                                                                                                                                                                                                                                                                                                                                                                                                                                                            | Date: September 29, 2025                                                                                                                                                     |
| FUNDING APPROVAL LETTER                                                                                                                                                                                                                                                                                                                                                                                                                                                                                                                                                                                                                                                                                                                                                                                                                                                                                                                                                                                                                                                                                                                                                                                                                                                                                                                                                                                                                                                                                                                                                                                                                                                                                                                                                                                                                                                                                                                                                                                   |                                                                                                                                                                                     |
